## Abstract

**Background:**

The side effects of chemotherapy, specifically chemotherapy-induced nausea and vomiting, are a concern for patients. To relieve these side effects, antiemetic drugs are recommended. However, some patients report that these drugs are not sufficiently effective. Moreover, patients with chronic disease, including cancer, are increasingly interested in complementary and alternative medicines, and express the desire for nonpharmacological treatments to be used in hospitals. Foot reflexology is a holistic approach that is reported to significantly reduce the severity of chemotherapy-induced nausea and vomiting in patients with breast cancer. Some of the chemotherapy treatments for patients with lung and digestive system cancer are moderately or highly emetic.

**Objective:**

The primary objective of this study is to assess the benefits of foot reflexology, together with conventional treatments, on the severity and frequency of chemotherapy-induced nausea and vomiting in patients with lung or digestive system cancer. The secondary objectives to be assessed are quality of life, anxiety, and self-esteem.

**Methods:**

This study is an open-label randomized controlled trial conducted over 22 months (18 months intervention and 4 months follow-up). Eligible participants are patients with a lung or digestive system cancer with an indication for platinum-based chemotherapy. Participants are randomized into two groups: conventional care with foot reflexology and conventional care without foot reflexology. Foot reflexology sessions (30 minutes) are performed on an outpatient or inpatient basis. It was estimated that 40 participants per group will be required. The benefits of foot reflexology will be assessed by comparing the relative change in the severity of nausea and vomiting, as assessed by a visual analogue scale, and the frequency of these side effects between the two groups. The secondary objectives will be assessed with the European Organization for Research and Treatment of Cancer Quality of Life Questionnaire; Hospital and Anxiety Depression Scale; and Body Image Questionnaire.

**Results:**

This study was approved by the regional ethics committee (Île de France X CPP) on April 3, 2018 (No. ID RCB 2018-A00571-54). Enrollment started in June 2018. Data analysis will be performed during the second quarter of 2020 and results will be published in the last quarter of 2020.

**Conclusions:**

The lack of knowledge regarding the efficacy and safety of foot reflexology limits oncologists to recommend it for this use. This study will provide evidence of the benefits of foot reflexology. If efficacy is confirmed, foot reflexology may be a promising complement to conventional antiemetic drugs.

**Trial Registration:**

Clinicaltrials.gov NCT03508180; https://www.clinicaltrials.gov/ct2/show/NCT03508180.

**International Registered Report Identifier (IRRID):**

DERR1-10.2196/17232

## Introduction

### Background

Patients with cancer are increasingly interested in complementary and alternative medicines (CAMs) [1]. According to the systematic review by Keen et al [2], the main reasons patients use CAMs are to treat their cancer, to treat the side effects of treatment, and to improve their quality of life. Patients with chronic disease, including cancer, express the desire for nonpharmacological treatments and CAMs be used in hospitals [3].

At the time of writing, the most frequently provided CAMs in private and public oncology centers in European countries are mind-body techniques, acupuncture, homeopathy, energy therapies, health promotion, traditional herbal medicine, as well as manipulation and body-based practices (kinesiology, osteopathy, physiotherapy, and reflexology) [4]. Foot reflexology is a holistic approach. A systematic review indicated that foot reflexology seems to be effective for patients with cancer but this field requires further rigorous research with a randomized controlled trial [5]. More specifically, foot reflexology improved the quality of life of patients in the palliative stage of cancer [6], significantly decreased pain intensity and anxiety in patients with metastatic cancer [7], and significantly decreased the perceived pain and anxiety of postoperative patients with gastric cancer and hepatocellular cancer [8]. Moreover, a significant decrease in chemotherapy-induced nausea and vomiting (CINV) was observed in patients with breast cancer who received reflexology treatments [9,10]. Foot reflexology, used concomitantly with conventional treatment, shows promise in decreasing the side effects induced by chemotherapy. In particular, it may decrease CINV, which is the side effect that concerns patients the most [11], as it decreases their overall quality of life [12,13] and induces metabolic complications [11]. In addition, CINV can lead to dose reduction, postponement of treatment, and even discontinuation of treatment [14], all of which can decrease the effectiveness of the treatment [15]. To control acute and delayed CINV, antiemetic drugs are prescribed; the main ones used are 5-hydroxytryptamine 3 receptor antagonists, dexamethasone, and neurokinin-1 inhibitor receptor antagonists [11,16,17]. But despite antiemetic therapy, CINV may persist [13]. In addition to the emetogenicity of the chemotherapy, various parameters may be associated, including risk factors (age, gender, alcohol use, history of motion sickness, and history of pregnancy-related vomiting) [12], treatment compliance [18] and the perceptual gap between health professionals and patients [19,20].

In 2018, in both sexes combined, lung cancer was the leading global cause of cancer death (18.4%), followed by digestive system cancer including colorectal (9.2%), stomach (8.2%), and liver (8.2%) [21]. According to national and international recommendations, adjuvant treatment for lung and digestive system cancer is platinum-based chemotherapy [22-26]. Anticancer therapy cisplatin has a high emetic risk (incidence of CINV >90%), while carboplatin and oxaliplatin have a moderate emetic risk (incidence of CINV is from 30% to 90%) [17].

### Objective

The aim of this study is to determine whether foot reflexology decreases the side effects induced by chemotherapy (specifically, CINV resulting from platinum-based chemotherapy) in patients with lung or digestive system cancer.

## Methods

### Trial Design

An open-label randomized controlled trial (RCT) will be carried out, in which patients are randomized to one of two groups at a 1:1 ratio: (1) conventional care with foot reflexology (40 patients) and (2) conventional care without foot reflexology (40 patients). Randomization is stratified on the type of cancer (digestive system or lung) and the presence or absence of metastases. The sponsor is the Hospices Civils de Lyon. The principal investigator is [name]. To design this trial, we used the CONSORT Statement for Randomized Trials of Nonpharmacologic Treatments [27].

### Eligibility Criteria of Participants

Eligibility requirements for this study are the following: patients aged ≥18 years; patients with lung cancer (eg, non–small cell lung carcinomas, small cell lung cancer, mesothelioma) or digestive system cancer (eg, colorectal cancer, pancreatic cancer, liver cancer); patients on platinum-based chemotherapy with or without radiation therapy concomitant (eg, digestive system cancer: FOLFOX, FOLFIRINOX, GEMOX, LV5FU2-CDDP; lung cancer: cisplatin-vinorelbine, pemetrexed-cisplatin, pemetrexed-carboplatin, carboplatin-paclitaxel); World Health Organization performance status ≤2; patients affiliated to the national social security system or equivalent; patients able to complete the questionnaires (comprehension of oral and written French language); and patients who provide written informed consent. The exclusion criteria are phlebitis; vena cava syndrome; weight loss >5% in the 3 months before inclusion date; uncontrolled pain; patients receiving morphine or morphine derivatives; brain metastases; patients receiving foot reflexology outside the study; patients under guardianship or curatorship or who have been deprived of their rights. All data will be collected from outpatients and inpatients.

### Description of Processes, Interventions, and Comparisons

The patients randomized to the intervention group will benefit from a foot reflexology session (30 minutes) at each chemotherapy session for four cycles. The reflexology sessions will be given during chemotherapy infusion every 2 or 3 weeks, depending on the chemotherapy protocol. The sessions will be administered by two qualified reflexologists (they were trained at the French school École des Techniques en Réflexologie).

In a meta-analysis study, Lee et al [28] determined that the optimal comparator is a control group with conventional care without foot reflexology or massage therapy.

Foot reflexology is CAM, based on the principle of acupressure, that helps the body restore homeostasis. It is a holistic approach that allows one to understand the body as a whole. Each part of the body is represented by a zone or reflex point on the foot. The reflexologist stimulates each reflex zone using specific thumb and finger techniques on the patient’s feet. Depending on the objective, the zones on the feet are stimulated using different types of pressure. During a session focused on the treatment of CINV, the reflexologist mainly stimulates the reflex points related to the digestive system, the lymphatic system, and kidneys to help the body eliminate toxins. The reflexology chart used in this clinical study is based on the one proposed by Eunice Ingham [29].

The reflex zones of the whole body are also found on the hands. During the first reflexology session, the reflexologist shows the patient the appropriate zones on the hands to relieve nausea. The patient will be able to stimulate these reflex points between each cycle if necessary (self-practice at home). Adherence of participants to reflexology is assessed with a diary. They have been instructed to use a diary every day between each cycle of chemotherapy to note episodes of nausea and vomiting. They also note if they took at least one antiemetic drug (on-demand treatment). If the patient uses self-massage, they note whether it has been effective.

The protocol of intervention was standardized by the reflexologists involved in this study. Over the course of the session, relaxation movements were incorporated after each stimulated reflex point. To calm nausea and vomiting, the reflexologist stimulated the upper and lower digestive reflex points, as well as smooth muscle reflex points (lymphatic system; kidneys and bladder; lungs; and thyroid and parathyroid). Encouraging deep relaxation to target anxiety involved the stimulation of the diencephalon reflex points, scapular belt reflex points, reflex points of the diaphragm, and reflex points of the spine.

### Enrolment, Screening, and Allocation

Participants will be enrolled by physicians at the Lyon Sud Hospital Centre thoracic and hepatogastroenterology departments. Eligible participants who wish to participate in the study are asked to sign a written informed consent form. The randomization procedure is performed by the Interactive Web Response System (IWRS) via ClinSight software (Ennov Clinical, version 7.5.710, Ennov Group). Participants are allocated to the intervention group (with foot reflexology) or to the control group (without foot reflexology) before starting their treatment. Clinical research assistants generate the random allocation sequence and assign participants to the intervention.

### Primary Objective

The primary objective is to assess the benefits of foot reflexology on CINV (from platinum-based chemotherapy) in patients with lung or digestive system cancer.

### Secondary Objectives

The secondary objectives are to assess the benefits of foot reflexology in terms of overall quality of life, anxiety, and self-esteem.

### Evaluation Criteria

#### Primary Outcome

The primary outcome is the relative change in the severity of nausea and vomiting, as assessed with a visual analogue scale (VAS). The patient is asked to mark their current nausea level on the horizontal line with anchor statements on the left (a happy face, no nausea=0 mm) and on the right (a very sick green face, paroxysm of nausea or vomiting=100 mm). Unlike vomiting, which is measurable by the number of episodes per day, nausea is a subjective experience. For that reason, we will use a VAS to evaluate the severity of nausea in patients [30]. For patients in the intervention group, this measurement will be done when the patient arrives at the outpatient or inpatient department and after the foot reflexology session, during the second cycle of chemotherapy. For patients in the control group, this measurement will be done when the patient arrives at the outpatient or inpatient department and before leaving the hospital, during the second cycle of chemotherapy. The assessment is performed by a nurse or clinical research assistant.

All patients will continue to receive standard antiemetic drugs (eg, 5-hydroxytryptamine 3 receptor antagonists, dexamethasone, and neurokinin-1 inhibitor receptor antagonists). According to chemotherapy protocols, oral antiemetic agents are included, and patients are instructed to complete the course.

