### Type of Statistical Analysis Used

Study data are entered into a password-protected Excel spreadsheet (version 14.0, Microsoft Corp) accessible only to the project manager. Quantitative data will be described for the entire population, using the following descriptive statistics: the number, the number of missing values, the mean, the standard deviation, the median, the interquartile range, and the range. Qualitative variables will be summarized for the entire population using the following descriptive statistics: the frequency and percentage for each category of the variable and the missing values (missing values will be counted but are not included in the denominator of the calculation of frequencies).

For the primary endpoint, comparison of the relative change in the VAS between the two groups will be performed using a linear model adjusted on the type of cancer (digestive system or lung) and the presence of metastases (randomization stratification factors). This model allows the estimation of the difference in mean relative variation of VAS between the two groups, adjusted on potential confounding factors, with a 95% confidence interval. The VAS score may be transformed satisfy the assumptions of the linear model. If the assumptions of the model cannot be verified, the comparison between the two groups will be done using the van Elteren test. Specific estimates of the difference in relative VAS variation between the groups will be provided for both types of cancer, and by metastatic status.

The comparison of the frequency of episodes of CINV between chemotherapy cycles between the two groups will be performed using a mixed effects Poisson model, integrating the number of intercycle days as offset. The model will consider the intervention group and stratification criteria as fixed effects, and will incorporate one random intercept per patient.

The proportion of chemotherapy cycles in which the patient took at least one antiemetic drug will be compared between the two groups using a mixed effect logistic regression model. The model will consider the intervention arm and stratification criteria as fixed effects, and will incorporate one random intercept per patient.

The comparison of quality of life and anxiety between the two groups will be done using a Wilcoxon test.

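### The primary outcome, relative change in VAS from arrival at cycle 2, has no value for a patient who arrives at 0 mm and is unstable just above 0 mm, and the sample size has almost no room for such patients

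*Protocol article*

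**What the plan says.** Under Primary Outcome, the protocol article defines the endpoint as a ratio: "The primary outcome is the relative change in the severity of nausea and vomiting, as assessed with a visual analogue scale (VAS". Patients mark their current nausea on a line with "anchor statements on the left (a happy face, no nausea=0 mm" and 100 mm at the right-hand end. For those allocated to reflexology, the timing is given as follows: "this measurement will be done when the patient arrives at the outpatient or inpatient department and after the foot reflexology session, during the second cycle". Control patients are measured on arrival and before leaving the hospital. The denominator is therefore the arrival score at cycle 2.

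Three other statements bear on how low that score may be:
- Description of Processes, Interventions, and Comparisons: "The reflexology sessions will be given during chemotherapy infusion every 2 or 3 weeks, depending on the chemotherapy protocol". Arrival at cycle 2 is thus two or three weeks after cycle 1.
- Primary Outcome: "All patients will continue to receive standard antiemetic drugs".
- Eligibility Criteria of Participants lists no requirement for nausea.

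Under Type of Statistical Analysis Used, "comparison of the relative change in the VAS between the two groups will be performed using a linear model", adjusted for cancer type and metastatic status. The VAS score may be transformed to meet the model assumptions. If these cannot be verified, the van Elteren test is used. The analysis set is the patients who completed the endpoint evaluation, in their allocated group.

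Sample Size takes mean improvements of 49.5% and 73.5%, a common SD of 32.2%, a two-sided 5% level and 90% power, and arrives at 40 per group. It states no allowance for patients without an evaluable outcome.

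**The concern.** A relative change needs a positive denominator, and the plan allows that denominator to be zero. A patient who arrives at 0 mm and leaves at 15 mm has completed both assessments and belongs in the stated analysis set, yet has no outcome value. Such patients must be dropped or given a value by convention.

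Just above zero the ratio exists but behaves badly. A few millimetres of movement, or of imprecision in marking the line, produce a very large percentage, and only on the worsening side.

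Any exclusion would also happen after randomisation. Allocation precedes treatment, the intervention group has a session at cycle 1, and patients learn hand self-practice there for use between cycles. If reflexology lowers nausea before cycle 2, more intervention than control patients could arrive at 0 mm, and the comparison would lose them unequally. At stake are who is in the primary comparison, how much a few patients with small starting scores weigh in it, and whether the planned power applies.

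**Working it through.** **1. The plan's own figure.** Inputs from Sample Size: difference 73.5 − 49.5 = 24 points, SD 32.2, two-sided 5%, power 90%.
- Standardised difference: 24 / 32.2 = 0.745.
- Normal approximation: n = 2 × ((1.960 + 1.282) / 0.745)² = 37.8, so 38 per group.
- Two-sample t-test: 38.8, so 39 per group.

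The stated 40 reproduces, with power 0.909 by t-test (0.915 by normal approximation). The margin is small. By t-test, 39 per group gives 0.901 and 38 gives 0.894. By normal approximation, 38 gives 0.901 and 37 gives 0.894. One or two patients per arm can be spared.

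**2. The outcome at and near 0 mm.** With arrival score A and second score S, improvement is 100 × (A − S) / A.
- A = 0: division by zero, so no value for any S.
- A = 2, S = 10: 100 × (2 − 10) / 2 = −400%.
- A = 5, S = 10: 100 × (5 − 10) / 5 = −100%.
- A = 60, S = 20: 100 × (60 − 20) / 60 = +67%.

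Improvement cannot exceed 100% (S = 0). Worsening has no comparable limit as A approaches 0.

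**3. Power if 0 mm patients are not evaluable.** The share is an assumption. The evaluable number is 40 × (1 − share), and the difference and SD are kept as planned.

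| Share at 0 mm | Evaluable per arm | Power (t-test) | Power (normal) |
|---|---|---|---|
| 10% | 36 | 0.877 | 0.885 |
| 20% | 32 | 0.835 | 0.846 |
| 30% | 28 | 0.782 | 0.796 |
| 50% | 20 | 0.632 | 0.654 |

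**4. Sensitivity of the SD to a small denominator.** Suppose one patient of 40 in each arm goes from 5 to 10 mm (improvement −100%), with the planned mean and SD in the rest. With p = 1/40, the variance in an arm with planned mean m is (1 − p) × 32.2² + p(1 − p)(m + 100)².
- Control (m = 49.5): 1010.9 + 544.8 = 1555.7, SD 39.4.
- Intervention (m = 73.5): 1010.9 + 733.7 = 1744.7, SD 41.8.
- Pooled SD: √((1555.7 + 1744.7) / 2) = 40.6. Expected difference: 24 × 0.975 = 23.4.
- Power at 40 per arm: about 0.72 (t-test) or 0.73 (normal).

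**5. Would an analysis in mm do better?** Illustrative simulation: 40 per arm, arrival score 1 mm plus an exponential with mean 25 mm, the plan's mean improvements and its 32.2% SD between patients, and reading noise on the second score.

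| Reading noise | Relative change, linear model | Second VAS in mm, adjusted for arrival |
|---|---|---|
| none | 90% | 66% |
| 5 mm | 28% | 58% |
| 10 mm | 11% | 40% |

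The arrival distribution and the noise are assumptions. The order depends on the noise, and the mm analysis does not reach 90% in any of these settings. In a similar set-up (exponential mean 30 mm, 5 mm noise, no zeros), a rank test on relative change had power 0.48 against 0.21 for the t-test.

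**The case against.** The strongest reply has four parts.

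*The article shows no arrival scores.* This stands. A reader might infer from the working that patients will be lost, that the 32.2% SD fails and that the 90% power is gone. The article does not support that. The SD comes from a cited study of percentage improvement on a VAS, and with few arrival scores near zero it could hold. Nor can the share at 0 mm be read off the Background statement that "carboplatin and oxaliplatin have a moderate emetic risk (incidence of CINV is from 30% to 90" per cent. Its complement, 10% to 70%, describes patients without CINV under these drugs, not patients free of nausea on arrival weeks later.

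*A rule for 0 mm may sit in an analysis plan that is not shown.* It may. But the article itself fixes both the ratio and the linear model on it, and a rule for exact zeros would leave the instability just above zero.

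*The fallbacks deal with it.* In part. Van Elteren limits the influence of extreme ratios but still needs a value for each patient. A transformation of the score, such as a shifted logarithm, could be defined at 0 mm. However, the article names none and allows transformation only to satisfy model assumptions.

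*The mm analysis has weaknesses of its own.* This stands. Arrival VAS at cycle 2 is measured after randomisation and may already carry a treatment effect, so adjusting for it can remove part of the benefit. A reader might also assume that the mm analysis is always more powerful. The simulation shows that it is not when improvement is truly proportional and noise is small.

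**Conclusion.** The definitional fault is firm and rests on the text alone: the primary outcome does not exist at a permitted starting score, is unstable just above it, and is not rescued by the fallbacks as worded. Any resulting exclusion would follow cycle-1 reflexology and may differ by arm, though nothing in the article shows that it does.

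The size is conditional. The sample-size arithmetic is correct. Power falls below 90% once about two or three patients per arm are not evaluable, and reaches about 88%, 84%, 78% or 63% at assumed shares of 10%, 20%, 30% or 50%. The supported conclusion is that the power can be lost, not that it is lost.

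**What to change.** Before the outcome data are examined:
- Define the primary outcome as the second cycle-2 VAS in mm. Analyse it with a linear model containing arm, arrival VAS, cancer type and metastatic status, and report the adjusted mean difference in mm with its 95% confidence interval. Include patients who start at 0 mm.
- State that this estimates the within-visit effect, because arrival VAS is a post-randomisation measure. Add a sensitivity analysis without that covariate.
- Make the van Elteren test on the mm score or the mm change the fallback.
- Keep relative change as a descriptive supplement, in patients above a stated arrival score.

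Cost: protocol and analysis-plan wording and a new power calculation, with no new data, since both readings are already collected. The percent-based 90% power no longer applies. It must be restated in mm from an assumed SD, because the article gives none. The headline result will be in mm rather than percent, and the mm analysis may be the less powerful one if improvement is truly proportional and measurement noise is small.

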### Sample Size

In a study reported by Billhult et al [35], the mean improvement for CINV (measured using a VAS) was 49.5% in the placebo group, and 73.5% in the massage group (with a common standard deviation of 32.2%). Assuming these same hypotheses, for a two-sided risk of 5%, it is necessary to include 40 patients per group to demonstrate a statistically significant difference between the two groups with a power of 90%.

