The comparison of self-image between the two groups will be done using a linear model adjusted on the baseline self-esteem evaluated with the Rosenberg scale. A possible transformation of the BIQ score will performed to satisfy the assumptions of the linear model.

The analysis will be performed according to the intention-to-treat principle, considering all patients that completed the endpoint evaluation in the group that was allocated to them by the randomization. The time point for the primary endpoint has been defined to minimize the risk of missing data.

For the primary endpoint, a secondary analysis will be performed per protocol, including patients with the endpoint assessment, and for whom the strategy allocated during randomization was fully implemented (ie, patients allocated to the foot reflexology group that did not receive four sessions of foot reflexology will be excluded from the analysis).

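### A reflexology patient who attends cycle 2 without a session has no scheduled second VAS and so leaves the intention-to-treat set, by a route that controls do not have

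*Protocol article*

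**What the plan says.** The primary outcome is the relative change in VAS between two readings at the second chemotherapy cycle. The Primary Outcome section times them by arm:

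- Reflexology: "this measurement will be done when the patient arrives at the outpatient or inpatient department and after the foot reflexology session".
- Control: "this measurement will be done when the patient arrives at the outpatient or inpatient department and before leaving the hospital".

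No other time is given for a patient allocated to reflexology who attends cycle 2 and has no session.

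Under Type of Statistical Analysis Used, the intention-to-treat analysis is defined as "considering all patients that completed the endpoint evaluation in the group that was allocated to them by the randomization". The only remark there on missing endpoint data is "The time point for the primary endpoint has been defined to minimize the risk of missing data". The per-protocol analysis then applies a further rule: "patients allocated to the foot reflexology group that did not receive four sessions of foot reflexology will be excluded from the analysis".

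On delivery, the section on processes and interventions says that sessions take place during the infusion, and that "The sessions will be administered by two qualified reflexologists".

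**The concern.** In one arm the second reading is tied to receipt of the randomised treatment. In the other it is tied to departure, which depends on no session. The analysis set is then conditioned on having that reading. The two rules together make inclusion in the primary analysis depend on treatment receipt in the reflexology arm only.

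This differs from ordinary missing data. The patient has come to hospital and could be assessed, but the schedule provides no assessment. Such patients are the ones an intention-to-treat analysis is meant to keep and a per-protocol analysis is meant to set aside. For a session missed at cycle 2, the written rules remove them from both.

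At stake is whether the primary comparison is still one of the groups formed by randomisation. If the reason for having no session is related to nausea, the remaining reflexology patients are a selected group. If it is unrelated, the estimate still describes patients who had session 2, and not all those to whom reflexology was offered.

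**Working it through.** **1. The rules side by side, for a patient who attends cycle 2**

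| Patient | Second VAS scheduled? | In the intention-to-treat set as written? |
|---|---|---|
| Reflexology, session given | Yes, after the session | Yes, if the reading is taken |
| Reflexology, no session | No time given | No, unless staff take a reading on their own initiative |
| Control | Yes, before departure | Yes, if the reading is taken |

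The problem is confined to cycle 2. A patient who misses only session 1, 3 or 4 still has the primary endpoint. A patient with no cycle-2 visit is lost in either arm and is not part of this point.

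**2. The plan's own figure**

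Inputs from Sample Size: mean improvement "was 49.5% in the placebo group, and 73.5% in the massage group", SD 32.2%, two-sided 5%, power 90%. The difference is 73.5 − 49.5 = 24.0 points.

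n per arm = 2 × (1.960 + 1.282)² × 32.2² / 24.0² ≈ 37.8, so 38 (normal approximation). The t-test solution is 38.8, so 39. At 40 per arm the power is 91.5% (normal) or 90.9% (t). The stated 40 per group is reproduced and is not in dispute.

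**3. Difference as allocated against difference as analysed**

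Let m be the share of reflexology patients who attend cycle 2 without a session, and x their mean improvement. Assume that 73.5% applies to those who have the session.

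- As analysed (these patients absent): 73.5 − 49.5 = 24.0.
- As allocated (these patients kept): (1 − m) × 73.5 + m × x − 49.5 = 24.0 − m × (73.5 − x).

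Both m and x are assumptions; the documents give neither.

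| m | x = 49.5 (like controls) | x = 0 (extreme) |
|---|---|---|
| 5% | 24.0 − 0.05 × 24.0 = 22.8 | 24.0 − 0.05 × 73.5 = 20.3 |
| 10% | 21.6 | 16.7 |
| 15% | 20.4 | 13.0 |

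The formula also settles the direction. The analysis as written overstates the as-allocated difference when x is below 73.5 and understates it when x is above.

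**4. If reflexology has no effect**

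Suppose the patients without a session would have improved k SD less than the other reflexology patients. The bias is m × k × 32.2 and the standard error is 32.2 × √(1/(40 − 40m) + 1/40). Type I error is by normal approximation. The power column is the t-test power for the planned 24.0 points with the reduced arm.

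| Lost of 40 | Power | Bias, k = 0.5 | Type I error | Bias, k = 1 | Type I error |
|---|---|---|---|---|---|
| 2 (5%) | 90.1% | 0.8 | 0.051 | 1.6 | 0.056 |
| 4 (10%) | 89.3% | 1.6 | 0.055 | 3.2 | 0.072 |
| 6 (15%) | 88.3% | 2.4 | 0.062 | 4.8 | 0.099 |
| 8 (20%) | 87.3% | 3.2 | 0.071 | 6.4 | 0.135 |

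Example, 4 lost and k = 1: 0.10 × 1 × 32.2 = 3.2 points. The loss of power is minor. Any material harm comes from selection.

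**The case against.** The strongest reply is that the Primary Outcome section describes the normal course of a visit. It does not say that a patient without a session goes unmeasured. A nurse or clinical research assistant takes the readings and could take one at departure, and a condensed article may leave such contingencies to the full protocol. It is fair that nothing forbids the reading, so a reader should not infer that the protocol requires these patients to go unmeasured. But the article does more than stay silent. It states the trigger for each arm and it states the completer condition, and these two rules produce the gap. A reading taken at staff discretion in an open-label trial is a poor substitute, and one not taken cannot be recovered at analysis.

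Three stronger readings are tempting, and the documents do not support them.

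- *The comparison is of session recipients with everyone randomised to control.* The completer condition applies to both arms, and a control without a departure reading also drops out. The reflexology arm has one additional route to exclusion.
- *The result is biased in favour of reflexology.* That needs sessions to be missed because of nausea, and those patients to improve less. Lack of a reflexologist could be unrelated to outcome, some patients may decline because they feel well, and a patient with high nausea on arrival has room to improve.
- *The effect could be overstated by as much as 85%.* The arithmetic is right (24.0 / 12.975 − 1), but it combines the highest assumed miss rate with no improvement in every such patient.

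The event may also be uncommon. Sessions are given during an infusion for which the patient is already present, and having two reflexologists offers some cover. The per-protocol rule shows that missed sessions are foreseen, but not how many fall at cycle 2. This limits the likely size and leaves the structural point intact.

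**Conclusion.** The concern holds in a limited form. Followed as written, the timing rule and the completer condition give reflexology patients a route out of the intention-to-treat set that controls do not have: attending cycle 2 without a session. Selection bias in the primary comparison may follow. Neither its direction nor its size can be established from the documents, which give no miss rate, no reasons and no outcomes for such patients.

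The figures are illustrations. The mild case (22.8–20.4 points against 24.0) rests on 5–15% missing session 2, on their improving like controls, and on 73.5% being the mean among recipients, which Sample Size does not specify. If those who miss are otherwise typical patients, that gap is between the effect of having the session and the effect of offering it, and type I error is not inflated. Inflation, 0.051 to 0.135 over the range examined, requires that those who miss would have done worse anyway. The zero-improvement case (20.3–13.0) is an outer bound for these miss rates, assuming no worsening, and not a forecast.

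The change is worth making because the gap affects the primary endpoint and costs little to close.

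**What to change.** In Primary Outcome, state that every patient who attends cycle 2 has the second VAS whether or not a session is given. Preferably take it at a session-independent time common to both arms, such as before departure from hospital. This closes the gap and also removes the difference in measurement time between arms. At a minimum, use the control-arm time for a reflexology patient who has no session; this closes the gap but leaves two measurement times within the reflexology arm.

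Record the reason whenever a session is not given. In the analysis section, state that these patients stay in their allocated arm for intention-to-treat, and that exclusion for non-receipt applies only to the per-protocol analysis.

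Enrolment began in June 2018, so some patients may already be past cycle 2. For them, report by arm how many attended, had a session and have both readings, and show the primary result over a range of values for those without a second reading.

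The cost is a sentence or two in the protocol and staff instructions, and a few extra VAS marks. The estimated effect may be smaller, because non-recipients are kept and because a departure reading may come later than one taken straight after the session.
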